## HLMA Research Protocol

For use by HMS, HSDM and Harvard Chan School  
Investigators

point 1 and after 6 months will be assessed by gas chromatography at the Harvard T.H. Chan School of Public Health, which provides high quality laboratory measurements to studies around the globe. The rest of the plasma and blood samples collection will be stored for future potential studies at Ohio University in the Edison Biotechnology Institute.

-Urine samples will be collected at the same time as blood samples. First spot morning urine will be obtained at home, after an overnight fast, following specific instructions for its collection (same as those given for routine laboratory analyses). Hydroxytyrosol and tyrosol will be measured by gas chromatography–mass spectrometry by Professors [name]’ experienced team at the University of Athens.

- Both blood and urine samples will be deidentified and coded, initially processed at a private company, Clinical and Translational Support (CTSL), Indianapolis. Blood samples will be kept cool and will be processed to separate plasma immediately after the withdrawal in a refrigerated centrifuge and then, working on ice, immediately aliquotting into cryovials and placing into -80°C storage. Shipping to the [name] and [name] labs will be done on dry ice via FedEx overnight service in a cardboard and Styrofoam cold shipping container. The remaining aliquots will be sent and storage at Ohio University.

- Stool samples: Stools samples will be collected with OMNIgene®•GUT kit that is an all-in-one system for easy self-collection and stabilization of microbial DNA from feces for gut microbiome profiling. The participants will self-collect fecal samples according to the standard instructions provided with the kit. The kit includes the a two-way mailing box with peelable label. The stool is considered exempt human specimens, and can be sent via the normal postal system using their mailing package. Once the samples arrive at Ohio University they will be processed following the instructions: <http://www.dnagenotek.com/ROW/pdf/PD-PR-00695.pdf>

The samples will be collected in Indianapolis at Public Safety Medical by trained and qualify staff. The first step of sample preparation will be conducted in the Clinical and Translational Support CTSL Laboratory.

### **Follow-up Assessments:**

Every consented participant (regardless of intervention assignment) will be requested to complete the following every 6 months over 4 additional visits after the baseline assessment over the two years of the study:

The comprehensive nutritional-lifestyle questionnaire will be repeated (detailed above), as will the anthropometric measures (height, weight and body fat and resting blood pressure) will be collected in the same manner as described above for the baseline assessment.

Every 12 months, the Fire department provided, annual occupational medicine examinations (part of the firefighters’ usual care unrelated to the present study) will be provided by Public Safety Medical as per existing IFD/ Fishers policies. For consented participants ONLY, the medical exam results will be transferred to the Harvard Chan research team using the same established coded data transfer methods as described above for the baseline assessment of the same data points.

Consented participants will be assigned to Group 1 (Phase 1 nutritional intervention) or Group 2 (No intervention) according to their fire station’s cluster randomization.

For the nested biomarkers study the recruitment of participants will start in phase II following the below timeline:

Figure1. Current parent study timeline and biomarkers proposal timeline (in orange, the proposed study timeline)

[figure not shown]

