## 1. Specific Aims

1. Develop a multi-pronged, Mediterranean Diet Nutritional Intervention (MDNI) behavior change strategies including: diet/lifestyle education; discounted access to key Mediterranean diet foods; electronic education platforms and reminders. MDNI components will be refined via surveys, literature review and local/national firefighter input including labor/management and fire service focus groups.

Hypothesis (1). Cost-effective, fire-service MDNIs will be developed for the cluster-randomized, career firefighter diet intervention.

2. Cluster Randomized Diet Intervention-Phase I- the Indianapolis Fire Department (IFD) has over 1,000 members. All 44 IFD firehouses will be cluster randomized into two groups and then individual members will be consented regarding study participation. Group 1 will receive an active 12-month MDNI, while Group 2 will receive no intervention. Firefighters categorized as "Administrative Staff" by the IFD will also be approached for participation and if they consent, be assigned to Group 1 because they are not assigned to specific firehouses.

3. Cluster Randomized Diet Intervention -Phase II: Group 1 will cross-over to "self-sustained continuation" for 12 months to examine persistence of behavior change during this less intense, self-directed maintenance diet intervention. Group 2 will cross-over to receive the MDNI for 6 months (assessing a shorter MDNI), followed by a final 6 months of self-sustained continuation. An additional neighboring fire department, Fisher's (IN), will have its 6 firehouses randomized to receive the MDNI (Group 3) or no intervention (Group 4) for six months, and then individual members will be consented regarding study participation. After 6 months, the 3 stations in the MDNI (Group 3) will cross-over to "self-sustained continuation" for the last 6 months to examine persistence of behavior change during this less intense, self-directed maintenance diet intervention. Group 4 will cross-over to receive the MDNI for 6 months (assessing a shorter MDNI).

4. A similar 12-month Cluster Randomized Diet Intervention in the six fire stations of the Fishers (IN) Fire Department with a cross-over by the control group to intervention after 6 months will also be done.

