**4. Study Design****4.1. Describe the study design type**

Prospective, cluster-randomized Mediterranean Diet Nutritional Intervention versus no nutritional intervention for 12 months; followed by cross-over of interventions for an additional 6-12 months. The additional participants from Fishers (IN) Fire Department will be studied for 12 months. The nested study for the evaluation of adherence biomarkers and the stool sample collection will last 6 months.

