The participants in the biomarkers nested study will be already participating in the Feeding America’s Bravest. The baseline collection time for the biomarkers coincide with the 1-year follow up. The second visit will be after 6 months of follow up or the original 18 months of follow up (see timeline in figure 1 and the second table below. Thus, the participants will be filling out the lifestyle/nutrition questionnaires/ anthropometrics and medical exam as explained previously in the protocol in each time point. The additional tests they will take are described below:

y,- Two EDTA blood collection tubes will be collected (<15ml of blood) in the fasting state (meaning no food or liquids except water for at least 12 hours before the appointment) at time point 12 and at 18 months of follow-up. Plasma and serum will be aliquoted, frozen at -80°C, stored and run in batches. Forty fatty acids will be analyzed including oleic, alphaE linolenic acid (w3), and alphaElinoleic (w6), which are reliable indicators of MUFA, tree nut and other healthy fat consumption. Analyses at time

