†Optional and only for habitual drinkers without alcohol-related health problems.

‡Sofrito is a sauce made with tomato and onion and/or garlic, slowly simmered with olive oil.

§Homemade sweets are preferable to store-bought or commercially-produced sweets.

||Discouraged.

JOEM • Volume 58, Number 3, March 2016

Participants may also have access to additional discounted food options during the course of the study as follows:

1. Discount coupons obtained directly from producers which can be redeemed at Kroger and other local stores. For example, Barilla pasta has pledged its support to provide coupons for “Barilla Plus”, a line of pastas which combine ALA-3- enriched whole grain and legume flours to produce a high fiber, higher protein product yielding delicious pasta that is more nutritious and promotes better glucose metabolism than typical pasta from refined flours.

2. “Starter” supplies of extra-virgin olive oil, avocados and nuts and for fire house kitchens at no cost, along with coupons and options for obtaining additional product at discounted prices directly through food companies partnering with the study.

3. Encourage and facilitate access to farmer’s markets and produce from local community gardens within the City of Indianapolis and surrounding area.

According to each participant’s preference, they may sign up for either email or text message encouragement and reminders during the intervention. For those opting in to this option, they will receive brief text or email messages 2-4 times per week reinforcing the healthy dietary and lifestyle principles as discussed above.

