## PHASE II

### Mediterranean Diet Nutritional Intervention for 6 months for Groups 2 and 3 (and 4 in the final 6 months).

This intervention will be exactly as described above for Phase I, but will last 6 months. Afterwards, over the final 6 months of the study, the participants from Group 2 in Phase 1 will be encouraged to maintain eating Mediterranean style on their own using the support of the discount program, the study website and the support of fellow firefighters and family.

**Group 2: No intervention.** Over the next 12 months (year two). Phase 1 Group 1 participants will be encouraged to maintain eating Mediterranean style on their own using the support of the discount program, the study website and the support of fellow firefighters and family.

The table below summarizes data collection from all consented firefighter participants across the timeline of the 2-year study. Fishers Department FF will be joined to the study in the 12 months of follow up of the original Feeding America's Bravest

| Questionnaires/Measurements        | Baseline | 6months | 12months | 18months | 24 months |
|------------------------------------|----------|---------|----------|----------|-----------|
| Nutrition/Lifestyle questionnaires | X        | X       | X        | X        | X         |
| Blood Pressure                     | X        | X       | X        | X        | X         |
| Height/Weight                      | X        | X       | X        | X        | X         |
| Waist circumference                | X        | X       | X        | X        | X         |
| Body composition (Tanita)          | X        | X       | X        | X        | X         |
| Medical exam results transfer      | X        |         | X        |          | X         |

: .

The table below summarizes data collection from a random subset of consented firefighter participating in the biomarker study

| Biomarker proposal                                   | Time point1
(Dec2017/Jan 2018) | Time point2
(June2018) |
|------------------------------------------------------|-----------------------------------|---------------------------|
| Blood sample collection (fatty acids measurements)   | X                                 | X                         |
| Urine sample collection (hydroxytyrosol and tyrosol) | X                                 | X                         |

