
**When:** Recruitment will begin as soon as possible following the study's approval by the IRB with the Fire Chief and Union President letter being sent out to all department members. In person recruitment as described above will follow shortly thereafter, on a schedule to visit all 44 IFD / 6 Fishers fire

stations during regular business hours as many times as needed to approach all members with potential interest. For the biomarkers study recruitment will start by the end of December 2017/January 2018. We expect this process to take 4-8 weeks.

**Where:** The Fire Chief and Union President letter will be sent by mail and email to IFD /Fishers members. The in-person recruitment will take place in each fire station as described above. The PSM researchers will then be visiting each IFD / Fishers fire station to speak with the firefighters about the study and offer them the opportunity to participate. These discussions will take place in common areas of the fire houses such as kitchen/dining area and living rooms, while the individual consenting and question/answer will take place in areas of the fire house that provide privacy.

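### Later biomarker recruits can give their month-12 baseline sample after the Phase II switch, and with less than six months to the June 2018 sample

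*Protocol*

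**What the plan says.** **Sampling.** Protocol section 4.6 (Baseline Assessment) states: "The baseline collection time for the biomarkers coincide with the 1-year follow up". For the second sample it says: "The second visit will be after 6 months of follow up or the original 18 months of follow up". Section 4.1 agrees on the length: "The nested study for the evaluation of adherence biomarkers and the stool sample collection will last 6 months". The biomarker table in the Phase II part of section 4.6 dates time point 1 as "Dec2017/Jan 2018" and time point 2 as June 2018.

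**Recruitment.** Section 4.6 (Follow-up Assessments) says: "For the nested biomarkers study the recruitment of participants will start in phase II following the below timeline". That timeline is Figure 1, which is missing from the copy reviewed. Section 6.1 adds: "For the biomarkers study recruitment will start by the end of December 2017/January 2018. We expect this process to take 4-8 weeks". It also sends the biomarker invitation together with the follow-up reminder.

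**Intervention.** Phase I is the first 12 months. In Phase II, Aim 3 says "Group 2 will cross-over to receive the MDNI for 6 months (assessing a shorter MDNI"), after which Group 2 has six months of self-directed continuation. Group 1 leaves the active programme but keeps the discounts, the website and peer support. While active, the Mediterranean Diet Nutritional Intervention (MDNI) may include starter "supplies of extra-virgin olive oil, avocados and nuts and for fire house kitchens at no cost".

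**Analysis.** Aim 5a compares the intervention arm with the control arm. Section 5.2 plans between-group and change analyses of the biomarkers, and Spearman coefficients against self-reported intake.

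**The concern.** Month 12, just before the switch, is the only biomarker time point at which 12 months of MDNI can be compared with none. Once Phase II is under way, Indianapolis has no untreated arm. Recruitment that opens in Phase II and runs for weeks lets some first samples fall after the switch. Group 2 may by then have received olive oil and nuts, foods that the urine and fatty-acid markers are meant to detect, while Group 1 is no longer in the active programme.

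Two analyses are exposed: the month-12 contrast between arms, and Group 2's before-after change. The second sample is also fixed to a calendar month, so the interval between samples shortens as the recruitment date moves later. Samples taken late cannot be repaired in the analysis.

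**Working it through.** **1. The plan's own six months.** One month is taken as 30.4375 days.
- 25 December 2017 to 30 June 2018: 187 / 30.4375 = 6.1 months.
- 31 December 2017 to 30 June 2018: 181 / 30.4375 = 5.9 months.
- 31 January 2018, the last day of the time point 1 window, to 30 June 2018: 150 / 30.4375 = 4.9 months.

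The stated interval is reproduced for early recruits with a late-June second visit. It is not reproduced across the whole window.

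**2. When Group 2's MDNI starts.** The study lasts 24 months (section 4.2). Group 2 has 6 months of MDNI and then the final 6 months of continuation (Aim 3; section 4.6, Phase II). So 24 - 6 - 6 = 12: the MDNI starts at month 12, with no slack. Section 6.1 agrees, since stations are told that they receive it either at once or after 12 months.

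**3. MDNI received before the baseline sample.** Assume that recruitment and Group 2's MDNI start on the same day and that the sample is taken on recruitment. Share of a 26-week MDNI already received:
- last recruit: 4/26 = 15% to 8/26 = 31%;
- average under even recruitment: 2/26 = 8% to 4/26 = 15%.

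**4. Time left for the last recruit.** Recruitment start plus 4 or 8 weeks, then days to the second sample.

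| Start | Length | Last first sample | To 30 June 2018 | To 1 June 2018 |
|---|---|---|---|---|
| 31 Dec 2017 | 4 weeks | 28 Jan 2018 | 153 days, 5.0 months | 124 days, 4.1 months |
| 31 Dec 2017 | 8 weeks | 25 Feb 2018 | 125 days, 4.1 months | 96 days, 3.2 months |
| 31 Jan 2018 | 4 weeks | 28 Feb 2018 | 122 days, 4.0 months | 93 days, 3.1 months |
| 31 Jan 2018 | 8 weeks | 28 Mar 2018 | 94 days, 3.1 months | 65 days, 2.1 months |

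Only the first row stays inside the protocol's December/January window for time point 1.

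**5. Direction of the effect.** After the switch, Group 2's markers should rise if the intervention works, and Group 1's should hold or drift down. The gap between arms at the first sample then narrows. Group 2's baseline is also raised, so its measured change shrinks. The documents give no time course for these markers, so the size of the attenuation cannot be derived from them.

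**The case against.** The strongest reply is that the protocol already intends a clean month-12 sample. Section 4.6 places it at the 1-year visit, the table dates it December/January, and section 6.1 sends the invitation with the follow-up reminder. Month 12 is itself the boundary between phases, so a visit labelled Phase II need not follow the intervention start. Figure 1 might show the order. In section 6.1, the word *by* may set a latest start date, and the 4-8 weeks could refer to recruitment in general rather than to the sub-study.

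Much of this stands, and it rules out stronger readings that a reader might infer:
- **Every baseline is contaminated, or nobody has six months.** Not supported. Early recruits can be sampled at the boundary with about six months to go.
- **Group 1's intervention has stopped.** Too strong. Only the active programme ends.
- **The gap falls to about 11 weeks.** This takes a 31 January start, the full 8 weeks and a mid-June visit (79 days), with a first sample well outside the stated window.
- **With a fast marker response, at least half of Group 2 would show little change.** Under even recruitment, the share recruited after a complete response is 1 - response time / recruitment length. For a 2-week response it is 50% (4-week recruitment) or 75% (8-week). For a 4-week response it is 0% or 50%. The range is 0-75%, so no such statement holds.

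What the reply does not remove is the gap in the rules. The 4-8 weeks directly follow the biomarker sentence, and no text requires the first sample to precede the switch. The sections on recruitment therefore permit what the sections on sampling do not intend. Dates in the figure would not resolve that conflict in the text.

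**Conclusion.** The point holds as a conflict of timing that affects later recruits. Sections 4.6 (Follow-up Assessments) and 6.1 allow recruitment into Phase II for 4-8 weeks. Section 4.6 (Baseline Assessment) and its biomarker table need a first sample at month 12 and a second six months later.

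If recruitment and Group 2's MDNI start together, the last Group 2 recruits may already have had 15-31% of their MDNI at baseline. With a 31 December start and a 30 June second visit, the last recruits have about 4.1-5.0 months instead of 6, and less with a January start or an earlier June visit. These figures assume that the first sample is taken on recruitment and that the 4-8 weeks refer to the biomarker study.

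The likely effect is attenuation of the month-12 contrast and of Group 2's before-after change. The questionnaire-validation (Spearman) aim does not need a clean contrast between arms and is not materially affected. Neither is the parent trial's Phase I comparison. The change should be made, but it concerns a nested aim only.

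**What to change.** Reconcile the recruitment statements in section 4.6 (Follow-up Assessments) and section 6.1 with the sampling times in section 4.6 (Baseline Assessment and the biomarker table):

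1. Send biomarker invitations ahead of the month-12 visit.
2. Require the time point 1 sample at that visit, before the MDNI starts at the participant's station in Group 2 and before the active programme ends in Group 1.
3. Schedule time point 2 at about 26 weeks from each participant's first sample, in place of a fixed June 2018.
4. Record each first-sample date relative to the station's switch, and base the month-12 between-group contrast on samples taken before it.

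The cost is small. Invitations go out some weeks earlier, and no visits or samples are added. Any late samples drop out of that one contrast but remain usable for questionnaire validation. Since section 6.1 stops recruitment at 30 per group, preventing late samples is better than excluding them.

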## PHASE I (first 12 months of the study) Group 2: No

### intervention.

#### **Mediterranean Diet Nutritional Intervention for 12 Months for Group 1.**

The extent to which consented participants personally engage in the MDNIs is voluntary, and the additional time commitment required for the study is nominal. The Mediterranean Diet intervention will include educational materials; opportunities for discounted access to healthy foods consistent with the Mediterranean diet (e.g. extra-virgin olive oil, nuts, fruits, vegetables, legumes, whole-unrefined grains, and lean proteins) for both participating firefighters and their families; peer education/support, on-line learning, and email and text message encouragement and reminders. Each of these pieces of the intervention is explained in further detail below.

Educational materials (online learning) will be provided via the study website; group educational sessions and written materials. Examples of our educational information include: a brochure with Mediterranean Diet recommendations, shopping list recommendations and sample recipes, tips to practice the Mediterranean Diet at both home and work and a firefighter-specific Mediterranean Diet Pyramid have been developed for this purpose. These materials may be supplemented as the study progresses to include additional modified Mediterranean Diet recipes based on the firefighters' and their families' preferences and requests (e.g. supply a modified recipe for healthy Mediterranean lasagna or chili based on a fire station's request); short videos; and links to other healthy eating materials. The videos may include: cooking demonstrations; talks with firefighter "champions" (brief interviews and commentaries from firefighters who are successfully practicing the Mediterranean diet) and similar content.

The initial and periodic group educational sessions with larger groups (up to 100 firefighters) will be led by the Harvard investigators and the local medical team (Public Safety Medical) and held in fire department classrooms. These will be followed-up by more frequent, smaller group (5-20 firefighters) diet and fitness sessions in fire house classrooms and kitchens by our Indiana-based dietitian and Health/Fitness Specialist, [name]. [name] is contracted with PSM and has a long experience working with firefighters. The sessions may include: didactic presentations, interactive discussions and cooking demonstrations that follow the general recommendations (see below).

Specific topics that we plan to address in the group educational sessions include:

1. Basic Mediterranean Diet principles;
2. The benefits of Olive oil and nuts and how to introduce them into the diet;
3. Overcoming Challenges while following a Mediterranean Diet;
4. How to plan a weekly menu and shopping list;
5. How to choose wisely when eating out (restaurants/parties);
6. Making smart choices regarding "Fast food".

We may also provide in-person chef-led, Mediterranean cooking demonstrations at fire stations in the intervention group. Some of the general educational sessions and cooking demonstrations may be videotaped or otherwise adapted for internet accessibility on the study website.

All of the educational sessions and materials will be centered on the principles and general recommendations outlined in the table below.

